### 3.3.3. Exit Criteria

The participants may exit the study for any of the following reasons:

1. Voluntarily withdrawal (due to withdrawal of informed consent, loss of informed consent capacity, lack of efficacy, intolerance, adverse events [AEs], etc.);
2. Poor compliance, inability to receive the vaccine as scheduled, or complete the study protocol;
3. Becoming pregnant or lactating during the treatment period;
4. Experiencing complications, AEs, serious AEs (SAEs), or special physiological changes occurring during vaccination that lead the investigator to judge further vaccination as unsuitable;
5. Any other condition deemed by the investigator as necessitating withdrawal from the study.

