### 3.3.2. Intervention assignment

Both the experimental and control groups will receive two doses of the inactivated COVID-19 vaccine, administered on day 0 (baseline) and day 25±3. A third booster dose will be given 6 months after the second dose.

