## 3.5. Participant timeline

Figure 1. The schedule of enrolment, interventions, and assessments.

| **Visits** | **Screening** | **V1** | **V2** | **V3** | **V4** | **V5** | **V6** | **V7** | **V8** | **V9** |
| --- | --- | --- | --- | --- | --- | --- | --- | --- | --- | --- |
| **Timepoint (month)** | **Day**  **-21~0** | **Day 0** | **1^st^** | **2^nd^** | **4^th^** | **7^th^** | **8^th^** | **10^th^** | **13^th^** | **16^th^** |
| **Time window (day)** |  | **± 3** | **± 3** | **± 15** | **± 15** | **± 3** | **± 15** | **± 15** | **± 15** | **± 15** |
| **ENROLMENT:** | | | | | | | | | | |
| Informed consent | × |  |  |  |  |  |  |  |  |  |
| Eligibility screen | × |  |  |  |  |  |  |  |  |  |
| Demographical characteristics | × |  |  |  |  |  |  |  |  |  |
| Medical history | × |  |  |  |  |  |  |  |  |  |
| Urine pregnancy test  (reproductive women) | × |  | × | × | × | × | × | × | × | × |
| Height, weight, blood pressure | × |  |  |  |  |  |  |  |  |  |
| Underarm temperature | × |  |  |  |  |  |  |  |  |  |
| Lab tests & Images*^#^* | × |  |  |  |  |  |  |  |  |  |
| **INTERVENTIONS:** | | | | | | | | | | |
| Allocation |  | × |  |  |  |  |  |  |  |  |
| Vaccination |  | × | × |  |  | × |  |  |  |  |
| 30 minutes’ observing |  | × | × |  |  | × |  |  |  |  |
| **ASSESSMENTS:** | | | | | | | | | | |
| Lab tests*** | × |  | × | × | × | × | × | × | × | × |
| Distribute/recycle diary cards |  | × | × | × | × | × | × | × | × | × |
| Safety (AEs) |  | × | × | × | × | × | × | × | × | × |
| Safety (SAEs) |  | × | × | × | × | × | × | × | × | × |
| Concomitant care |  | × | × | × | × | × | × | × | × | × |
| Humoral immunoassays |  | × | × | × | × | × | × | × | × | × |

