## 3.10. Statistical consideration

### 3.10.1. Analysis of population and missing data

**Full Analysis Set (FAS):** According to the intention-to-treat (ITT) principle, this study aims to include as many participants as possible. Participants who did not complete all three doses of vaccination will be excluded.

**Per-Protocol Set (PPS):** Based on the FAS population, participants with poor compliance will be excluded. Specifically, this set excludes individuals who participated in follow-up no more than six times.

**Safety Set (SS):** Participants with at least one vaccination record and measured AEs/SAEs correspondingly.

**Missing Data Processing:** The missing data on demographic information, safety indicators, and immunogenicity indicators for the FAS and PPS populations will not be imputed.

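### Exit criterion 2 lets undefined non-compliance end follow-up as well as vaccination, and the vaccination schedule it refers to is stated in two ways that barely overlap

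*Protocol*

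**What the plan says.** **Exit.** Section 3.3.3 opens with "The participants may exit the study for any of the following reasons" and gives as its second reason "Poor compliance, inability to receive the vaccine as scheduled, or complete the study protocol". It sets no threshold for compliance, does not say which schedule is meant, and provides for no visits after exit.

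**Analysis sets.** Section 3.10.1 deals with compliance at the per-protocol step: "Based on the FAS population, participants with poor compliance will be excluded". The measure is attendance, with six follow-ups or fewer leading to exclusion. Dose timing is not mentioned. The same section removes anyone without all three doses from the full analysis set (FAS). It admits to the Safety Set anyone with one vaccination record and corresponding adverse-event data. Missing data in the FAS and per-protocol set are not imputed.

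**Schedule.** Section 3.3.2 has the first two doses "administered on day 0 (baseline) and day 25±3" and then says "A third booster dose will be given 6 months after the second dose", with no window of its own for dose 3. The section 3.5 timeline marks vaccination at V1, V2 and V5. It places these at day 0, month 1 and month 7, each with a window of three days either side: "Time window (day) | | ± 3 | ± 3 | ± 15 | ± 15 | ± 3".

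**The concern.** Stopping vaccination and leaving the study are different events, and the protocol merges them. A participant who misses visits or a dose date may still be willing to give blood and report events. If that participant is exited, everything after that point is lost.

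Three features make the loss a possible source of bias as well as of lower precision:

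- The ground is undefined and applied at discretion in a study that the Trial Summary describes as open and non-randomized.
- The groups compared are age groups. The Revision History (section 7.1) says that most participants are elderly, that they resist frequent blood collection, and that this lowers their willingness to be followed up. Removal tied to compliance could therefore fall unequally on the two groups.
- The primary endpoint is safety in the month after each dose, and titres are planned out to month 16. Early exit takes participants out of later assessments of both kinds.

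The reference to a schedule adds a second difficulty. An investigator who applies the criterion must know which dates count, and the protocol gives two sets.

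**Working it through.** **Step 1. What exit does to each analysis set (sections 3.3.3, 3.10.1 and 3.11).**

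- *Exit before dose 3:* the participant is outside the FAS, and hence the per-protocol set, because of the three-dose rule. Safety data already collected stay in the Safety Set.
- *Exit after dose 3:* the participant stays in the FAS, but with no titres after exit. Exit also stops the count of follow-ups that decides per-protocol membership.
- *Either case:* section 3.11 follows recorded adverse events until they are finalized. What is lost is newly arising events, later laboratory tests and later titres.

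**Step 2. The two dose-3 schedules in days.** Let *m* be the length of a month in days.

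- Section 3.3.2: dose 2 on days 22 to 28 (25 ± 3), so dose 3 on days 22 + 6*m* to 28 + 6*m*.
- Section 3.5: V5 at 7*m* ± 3.

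| *m* | Section 3.3.2 | V5 window | Common to both |
|---|---|---|---|
| 28 | 190–196 | 193–199 | days 193–196 (4 of 7) |
| 30 | 202–208 | 207–213 | days 207–208 (2 of 7) |
| 30.4375 | 204.6–210.6 | 210.1–216.1 | about 0.6 day |
| 31 | 208–214 | 214–220 | day 214 (1 of 7) |

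Dose 2 exactly on day 25 gives dose 3 on day 25 + 180 = 205 with 30-day months, two days before V5 opens. With 28-day months it gives day 25 + 168 = 193, the first day of the window.

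**Step 3. Where the mismatch starts.** A dose 3 on day d + 6*m*, with dose 2 on day d, lies within 7*m* ± 3 exactly when d lies within *m* ± 3. That is also the condition for dose 2 to fall in the V2 window. With 30-day months, dose 2 is allowed on days 22–28 by section 3.3.2 and on days 27–33 by the timeline. Dose 3 inherits this difference.

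**Step 4. True calendar months.** For a first dose on 1 July 2021:

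- Section 3.3.2: dose 2 on day 22, 25 or 28, plus six calendar months, gives 23, 26 or 29 January 2022.
- Section 3.5: seven months ± 3 days gives 29 January to 4 February 2022.
- One date is common to both.

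The protocol gives 1 July 2021 as the enrolment date but no accrual period, so I assume one. First doses on each of the 184 days from July to December 2021, with dose 2 on each of days 22–28 equally weighted, give 184 × 7 = 1,288 implied dose-3 dates. The number of permitted dose-2 days that lead to a dose 3 inside V5 is 1 for 118 start dates, 2 for 61, 3 for 1 and 4 for 4.

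- Dose-3 dates inside V5: 118 + 122 + 3 + 16 = 259, and 259/1,288 = 20.1%.
- With dose 2 exactly on day 25: 4 of 184 start dates.
- Over a full year of start dates from 1 July 2021 the counts are 212, 122, 2 and 29: (212 + 244 + 6 + 116)/(365 × 7) = 578/2,555 = 22.6%.

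The result therefore depends little on the assumed accrual period.

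**The case against.** The case against has several parts, and much of it stands.

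*Exit and per-protocol exclusion are different mechanisms.* This is right. They do not contradict each other, and section 3.10.1 says nothing about off-schedule dosing. The point is about data lost through exit.

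*The criterion does not say that a dose outside a visit window leads to exit.* Also right. A reader might infer that a participant dosed on target under section 3.3.2 qualifies for exit under section 3.5. But the list is permissive, inability to be vaccinated is not the same as a mistimed dose, and no section makes a window deviation a trigger.

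*No analysis is undermined as a test of compliance.* One might suppose that reporting immunogenicity in both sets is meant to show the effect of compliance. Section 3.10.2 plans both analyses but states no such comparison.

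*Safety data survive.* In part. Safety Set membership needs only one dose with event data, and recorded events are followed to their end. New events and later laboratory values after exit are still not provided for.

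*The 20% does not measure harm.* Correct. It is an overlap of dates and says nothing about how many participants are exited. It also takes six months as exact, although section 3.3.2 gives dose 3 no tolerance of its own. Nominally the schedules agree, since month 1 plus six months is month 7. The difference comes from setting day 25 against month 1.

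*Discretion would remain.* The last exit reason leaves withdrawal to the investigator's judgement whatever is done about the second. That limits what the change can achieve but does not argue against it.

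**Conclusion.** The point holds in a limited form. Section 3.3.3 allows undefined non-compliance to end follow-up, where section 3.10.1 already has a way to handle compliance in the analysis. The data lost are later laboratory values, new adverse events and titres. The loss may be uneven between age groups; the Revision History makes that plausible but does not show it. How many participants would be exited cannot be derived from the protocol.

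Separately, sections 3.3.2 and 3.5 disagree on the timing of doses 2 and 3. For dose 3 the overlap is 2 of 7 days with 30-day months, 1 of 7 with 31-day months and 4 of 7 with 28-day months. In calendar months it is about 20% of implied dates, under the assumed July–December 2021 accrual and equal weighting of dose-2 days. The exit criterion inherits this ambiguity.

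The change is worth making because it costs little and reduces a possible bias. The documents do not support a claim that the protocol requires on-plan participants to be removed.

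**What to change.** 1. In section 3.3.3, separate stopping vaccination from leaving follow-up. When vaccination stops remains for the investigators to decide.
2. Record poor compliance, off-schedule dosing and incomplete procedures as protocol deviations. Keep participants who still consent on the section 3.5 visits.
3. Keep their data in the Safety Set and, if they received all three doses, in the FAS. Under-dosed participants cannot enter the FAS while the three-dose rule stands. Handle compliance through per-protocol membership, as section 3.10.1 already does.
4. Reconcile sections 3.3.2 and 3.5 to one anchor and one window for doses 2 and 3, and tie the exit wording to them. The investigators decide which.

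The cost is protocol wording and a deviation code in the case report form, with no visits beyond those planned. The small downside is more incomplete records in the analysis sets. Participants who withdraw consent or cannot be reached are lost either way.

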## 3.4. Outcomes

### 3.4.1 Primary endpoint measures

- Safety profiles within one month after each vaccination dose, including:

1. The incidence of adverse events;
2. Liver function;
3. Kidney function;
4. Blood glucose;
5. Blood lipids;

- The definition and grade of AEs were evaluated according to the Common Terminology Criteria for Adverse Events, version 5.0:

1. Grade 1 (mild) - asymptomatic or mild symptoms, clinical or diagnostic observations only, intervention not indicated;
2. Grade 2 (moderate) - minimal, local, or non-invasive intervention indicated, limiting age-appropriate instrumental activities of daily living (ADL);
3. Grade 3 (severe or medically significant but not immediately life-threatening) - indication for hospitalization or prolongation of hospitalization, disabling and limiting self-care ADL.

### 3.4.2 Secondary endpoint measures

- Immune protection of the participants:
  - - The titers of neutralizing and anti-receptor binding domain (RBD) antibodies at the baseline and the 1^st^, 2^nd^, 4^th^, 7^th^, 8^th^, 10^th^, 13^th^, and 16^th^ months after the first vaccination in each study group.

## 3.5. Participant timeline

Figure 1. The schedule of enrolment, interventions, and assessments.

| **Visits** | **Screening** | **V1** | **V2** | **V3** | **V4** | **V5** | **V6** | **V7** | **V8** | **V9** |
| --- | --- | --- | --- | --- | --- | --- | --- | --- | --- | --- |
| **Timepoint (month)** | **Day**  **-21~0** | **Day 0** | **1^st^** | **2^nd^** | **4^th^** | **7^th^** | **8^th^** | **10^th^** | **13^th^** | **16^th^** |
| **Time window (day)** |  | **± 3** | **± 3** | **± 15** | **± 15** | **± 3** | **± 15** | **± 15** | **± 15** | **± 15** |
| **ENROLMENT:** | | | | | | | | | | |
| Informed consent | × |  |  |  |  |  |  |  |  |  |
| Eligibility screen | × |  |  |  |  |  |  |  |  |  |
| Demographical characteristics | × |  |  |  |  |  |  |  |  |  |
| Medical history | × |  |  |  |  |  |  |  |  |  |
| Urine pregnancy test  (reproductive women) | × |  | × | × | × | × | × | × | × | × |
| Height, weight, blood pressure | × |  |  |  |  |  |  |  |  |  |
| Underarm temperature | × |  |  |  |  |  |  |  |  |  |
| Lab tests & Images*^#^* | × |  |  |  |  |  |  |  |  |  |
| **INTERVENTIONS:** | | | | | | | | | | |
| Allocation |  | × |  |  |  |  |  |  |  |  |
| Vaccination |  | × | × |  |  | × |  |  |  |  |
| 30 minutes’ observing |  | × | × |  |  | × |  |  |  |  |
| **ASSESSMENTS:** | | | | | | | | | | |
| Lab tests*** | × |  | × | × | × | × | × | × | × | × |
| Distribute/recycle diary cards |  | × | × | × | × | × | × | × | × | × |
| Safety (AEs) |  | × | × | × | × | × | × | × | × | × |
| Safety (SAEs) |  | × | × | × | × | × | × | × | × | × |
| Concomitant care |  | × | × | × | × | × | × | × | × | × |
| Humoral immunoassays |  | × | × | × | × | × | × | × | × | × |

# Including hepatitis B serologic, alpha-fetoprotein (AFP), carcinoembryonic antigen (CEA), Anti-HCV, HIV antibody, TPHA, electrocardiogram (ECG), chest x-ray, abdominal ultrasound (liver, gallbladder, spleen, pancreas, kidney). * Including liver and kidney function, blood glucose, and blood lipids.

## 3.6. Sample size

The target sample size is 300 participants. The allocation ratio will be 2:1, with 200 participants in the elderly experimental group (aged 60–80) and 100 participants in the younger control group (aged 18–59).

## 3.7. Recruitment

Participants will be recruited exclusively from two designated COVID-19 vaccination hospitals: the Fifth Medical Center of Chinese PLA General Hospital, Beijing; and the Hunyuan County People's Hospital, Shanxi Province. No other recruitment strategy (*e.g.*, advertisement) will be adopted in this study.

## 3.8. Allocation and vaccine management

### 3.8.1. Allocation

The participants will be assigned to either the experimental or control group in a 2:1 ratio based on age.

### 3.8.2. Vaccine management

**Storage conditions:** All study vaccines must be stored securely, following their specific storage requirements before distribution. Each clinical research unit will designate a specific person responsible for vaccine storage and distribution and will keep detailed records. Expired vaccines are not to be used, and attention must be paid to risks such as fire, theft, and damage from heat, mildew, insects, or rodents.

**Notes:** Vaccines should always remain in their original packaging until use. Before administering a vaccine, one should check that the packaging is intact; the vaccine should not be used if the seal is damaged or missing. All unused vaccines and their packaging should be saved.

**Vaccine inventory**: It is the investigator’s responsibility to ensure that vaccine quantities align with those registered and to maintain and record vaccine registration. In accordance with regulatory requirements, the investigator or designee must keep records of vaccine delivery throughout the entire research process, including records of the amount of research vaccine received, stored, and/or distributed, and the amount of vaccine returned by the participant to the research center.

## 3.9. Data collection and management

The data for this study will be recorded and managed through an electronic data capture system. Before locking the database, data managers will review and discuss the data with principal investigators and clinical research partners and then produce a data management report. This scheme provides only general requirements for data management.

1. Completed case report forms are reviewed by clinical investigators and supervisors and subsequently submitted to the data statistics unit for data entry and management. Documentation of all processes is required.
2. Data entry and management are the responsibility of the data administrator of the statistical unit. The electronic database will be used for these purposes. To ensure data accuracy, double-entry and proofreading are to be carried out independently by two data administrators. If there are queries in the case report form (CRF), the data manager will fill in a question form and send it to the investigator via the supervisors. The investigator is expected to respond promptly. The data manager will modify, confirm, and enter the data according to the investigator’s answer and may resend the query form if necessary.
3. After data review and database confirmation, the database will be locked by the principal investigator, clinical research partners, and statistical analysts.
4. Next, the statistical plan will be discussed by the principal investigator, statistician, and clinical research partner. Modifications to the database after locking can only be made with the written consent of the clinical research leader, clinical research partner, statistician, or data manager.
5. After the database is locked, the data manager will import it into the designated database and submit it to the statistician for statistical analysis. The statistician will subsequently write the statistical analysis report.

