| Key eligibility criteria | **Inclusion criteria**   1. Signed informed consent; 2. In females, the urine pregnancy test was negative; 3. At least 6 months of follow-up was completed; 4. HBsAg, anti-HCV, HIV, treponema pallidum hemagglutination assay (TPHA) screening was negative; 5. Armpit temperature was ≤37.0℃; 6. The young group was aged 18–59 years, and the elderly group between 60–80 years.   **Exclusion criteria**   1. In females, the urine pregnancy test positive; 2. Pregnant or lactating women; 3. Known allergies to certain components of these two vaccines; 4. Patients with serious chronic diseases or advanced diseases such as high blood pressure, diabetes, asthma, thyroid disease, *etc*. which cannot be controlled by drugs; 5. Those suffering from thrombocytopenia, hemorrhagic disease or thrombotic disease; 6. Those with congenital or acquired angioedema/neuroedema; 7. Those with a history or family history of convulsions, epilepsy, encephalopathy, other progressive neurological diseases, and psychiatric disorders; 8. Lymphadenopathy； 9. Lymphoma, leukemia and other systemic malignancies; 10. Autoimmune disease; 11. Chronic diseases with cute exacerbation or acute infectious diseases and fever. |
| Study design | Study type: Prospective real-world interventional trial  Allocation: Open, non-randomized  Intervention model: Parallel group  Primary purpose: Prevention |
| Date of enrolment | July 1, 2021 |
| Target sample size | 300 (200 in the elderly group, 100 in the young group) |
| Recruitment status | Recruited |
| Primary outcomes | **Primary endpoint measures**   - Safety profiles within one month after each vaccination dose, including:   1. The incidence of adverse events;   2. Liver function;   3. Kidney function;   4. Blood glucose;   5. Blood lipids. - The definition and grade of adverse events (AEs) were evaluated according to the Common Terminology Criteria for Adverse Events (CTCAE), version 5.0:  1. Grade 1 (mild) - asymptomatic or mild symptoms, clinical or diagnostic observations only, intervention not indicated; 2. Grade 2 (moderate) - minimal, local, or non-invasive intervention indicated, limiting age-appropriate instrumental activities of daily living (ADL); 3. Grade 3 (severe or medically significant but not immediately life-threatening) - indication for hospitalization or prolongation of hospitalization, disabling and limiting self-care ADL. |

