## 4.2. Protocol amendments

Any major changes, such as alterations to study objectives, study design, participant population, sample sizes, study procedures, or outcomes that might impact the potential benefit or risk to participants, will require a formal amendment to the protocol and approval from the IRB.

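### Section 3.9 puts discussion of the statistical plan after database lock in an open trial, and lets any one of four roles consent to changing locked data

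*Protocol*

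**What the plan says.** Section 3.9 of the protocol sets out data handling in an introductory paragraph and five numbered steps.

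- **Before lock.** The introduction says that "data managers will review and discuss the data with principal investigators and clinical research partners", and that a data management report follows.
- **Step 3, lock.** "After data review and database confirmation, the database will be locked by the principal investigator, clinical research partners, and statistical analysts".
- **Step 4, plan.** "Next, the statistical plan will be discussed by the principal investigator, statistician, and clinical research partner".
- **Step 4, changes after lock.** Modifications "can only be made with the written consent of the clinical research leader, clinical research partner, statistician, or data manager".
- **Step 5, hand-over.** "After the database is locked, the data manager will import it into the designated database and submit it to the statistician for statistical analysis".

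The trial summary describes the design as "Allocation: Open, non-randomized", and section 3.8.1 assigns participants to groups by age.

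**The concern.** A statistical plan protects the reader because it is settled by people who do not yet know which choice favours which result. In a blinded trial, lock comes before unblinding, so a late plan may still be made without knowledge of group. Here there is no blind to break. Group is age, and any listing that carries age shows the group. If the plan is taken up after lock, by people who have already discussed the data, any choice still open can be made with the data in view. The nominal P<0.05 and the 95% confidence intervals attached to such a choice then lose their usual meaning.

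The second part is separate and does not depend on timing. Lock is meant to fix the data that will be analysed. If one person's consent is enough to alter them afterwards, lock gives little assurance, and this applies to every endpoint, including the primary safety endpoint.

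**Working it through.** The protocol offers no figure to reproduce and no arithmetic settles the point. The check sets the relevant passages side by side.

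**1. Order of events.** Read in sequence, section 3.9 gives: data review with investigators and partners, lock (step 3), discussion of the statistical plan (step 4), hand-over to the statistician and analysis (step 5). Step 4 begins with a word of sequence, so the order is stated and not merely an effect of list layout. No other section says that the plan is final before lock or before the data are reviewed.

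**2. Who has seen what.** Three parties discuss the plan: principal investigator, statistician and clinical research partner. Two of them, the principal investigator and the research partner, also take part in the pre-lock data discussion. No blinded or pooled review is described.

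**3. Consent after lock.** Lock is an act of three parties: principal investigator, research partners and statistical analysts. Reopening the data names four roles joined by "or". The minimum number of consents needed, as written, is therefore 1 of 4, and the data manager alone would suffice.

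**4. What the protocol already fixes.**
- Sections 3.4.2 and 3.5 list the visits.
- Section 3.10.1 defines FAS, PPS and SS and rules out imputation for FAS and PPS.
- Section 3.10.2 assigns safety to SS and immunogenicity to both FAS and PPS. It names chi-square or Fisher tests for proportions and the Mann-Whitney test for laboratory values and titres, and sets two-sided testing at 0.05.

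**5. What it leaves open.**
- Antibody-positive rates are compared between groups, but no titre threshold for positivity is given.
- The logistic regression screens baseline characteristics at P<0.1, but names neither the dependent variable nor a definite list of candidates.
- The pseudovirus subset has no stated size. Selection requires complete data through month 16, so it depends on follow-up. It also requires no significant age difference between groups whose age ranges, 18–59 and 60–80, do not overlap, so someone will have to decide how to apply that condition.
- Immunogenicity is analysed in both FAS and PPS, and neither is said to lead if they disagree.

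**6. Whether another rule closes the gap.** Section 4.2 requires a formal amendment for major changes such as "alterations to study objectives, study design, participant population, sample sizes, study procedures, or outcomes". These are examples and not a closed list, but analysis methods are not among them.

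**7. Supporting sign.** The revision history dates the final version January 26, 2022. Section 3.10.2 nevertheless plans an analysis of infection status at the end of 2022, and describes some methods in the past tense. This suggests, without proving it, that some analysis text was written after that date.

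**The case against.** The case on the other side is substantial and narrows the point in five ways.

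- **Timing of the plan itself.** A reader might infer that the plan is first written after lock. The text says only that it is discussed then. It excludes no earlier version, and section 3.9 calls itself a general outline of data management. A separate SAP may exist with an earlier sign-off date; it is not at hand.
- **Knowledge of results.** A reader might infer that everyone involved has seen outcomes by group. The protocol does not say so. Open allocation means that group is known, not that antibody results have been tabulated by group. The pre-lock review leads to a data management report, and in list order the plan discussion still precedes formal analysis. The text supports only that investigators and partners have discussed open data.
- **Extent.** Most of the analysis is not open, as step 4 of the working shows. The P<0.1 screening rule is data-driven whenever the plan is signed, so changing the order of steps would not cure it.
- **A tempting number.** With 2 antibodies at 9 visits there are 18 titre comparisons, and 1 − 0.95^18 = 0.60 is the chance of at least one P<0.05 if all were null and independent. This measures multiplicity and would be the same with a plan signed before lock. Repeated titres in the same people are also correlated, and one of the 9 visits is baseline. It does not measure this defect.
- **Post-lock changes.** Consent must be written, step 1 asks that processes be documented, and "or" may be loose drafting for joint consent.

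All of this stands as a limit on the point. None of it removes the two stated rules: the discussion follows lock, and one consent suffices as written. No other section corrects either.

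**Conclusion.** The point holds in a limited form. Section 3.9 orders the plan discussion after lock in an open, non-randomised trial whose investigators and partners have already discussed the data, and it permits post-lock changes on 1 of 4 consents.

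The timing defect reaches the four open choices listed in the working, and any fixed choice that might be revised at that discussion. It does not reach the analysis as a whole. The consent rule reaches the entire database. The documents give no basis for putting a number on the bias.

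Two assumptions carry the conclusion: that step 4 means what its opening word says, and that no signed plan predates lock. If such a plan exists and settles the four choices, the timing part reduces to correcting the wording of section 3.9, while the consent part stands. This is a defect that should be corrected, short of one that must be resolved before the trial's results can be used.

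**What to change.** 1. Reverse steps 3 and 4 of section 3.9. State that the statistical plan is finalised, signed and dated before lock and before any between-group tabulation. It should fix the positivity threshold, the outcome and candidate covariates of the logistic regression, the size and selection rule of the pseudovirus subset, and whether FAS or PPS leads for immunogenicity.
2. Replace the single-consent wording with joint written consent of the principal investigator, statistician and data manager for any change after lock, with an audit trail.
3. Label as post hoc any analysis decision made after lock, or already made with the data in view, and give its date.

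The cost is a few lines of text, with no effect on participants or data collection. One caveat applies: the trial summary lists recruitment as done, so it may be too late to sign a plan ahead of all tabulation. In that case, the third step is what remains available, and it should be applied openly. If a signed plan already exists, cite its date in section 3.9.
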